### Economic evaluation methods

This study component will address aim 6.

#### Population

The economic evaluation will synthesise relevant service and population level resource use data.

#### Data collection

Program and associated implementation related resource use will be estimated using service and project records, including implementation diaries. Staff time will be costed using estimates of salary ranges, while the cost of materials, equipment, consumables and travel will be valued using market prices. Potential cost savings from reduced emergency department presentations and overnight hospitalisations in the post-implementation period will be estimated using an approach that is consistent with the effectiveness analysis.

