**Methods:**

A community-engaged hybrid effectiveness-implementation study design will focus on the tailored implementation of Navicare at three new sites as well as monitoring implementation at an existing site established since 2021. Study outcomes assessed will include sustained access as the co-primary outcome (measured using access to Navicare mental health referral services) and Proctor’s Implementation Outcomes of feasibility, acceptability, appropriateness, adoption, fidelity, implementation cost, and sustainability. Data collection for the implementation evaluation will include service usage data, community consultations, interviews, and workshops; analysed using mixed methods and guided by EPIS and other implementation frameworks. Pre-post effectiveness and cost-consequence study components are embedded in the implementation and sustainment phases, with comparison to pre-implementation data and value assessed for each EPIS phase using hospital, service, and resource allocation data. A scaling up strategy will be co-developed using a national roundtable forum in the final year of the study. Qualitative exploration of other aspects of the study (e.g., mechanisms of action and stakeholder engagement) will be conducted.

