Appropriateness	The extent to which the Navicare service is perceived as suitable, compatible, useful and practical and aligns with the values, needs and experiences of the target population and context. ^a, b^	Qualitative: Interviews and/or focus groups with service users, providers and community members; Care Navigator implementation diaries; and field notes, relevant documents and observation Timepoint: As per feasibility
Adoption	Service level assessment of actions to engage with or use the Navicare service ^a^, including frequency, timing and quality of communication and referrals, occasions of service (number, timing), % available services accessed by service user (e.g., counselling), and extent of service provision	Quantitative: Navicare service and project data Qualitative: Care Navigator implementation diaries, project records and meeting minutes Timepoints: As per feasibility
Fidelity	The extent to which the Navicare service is delivered and received as intended. This includes the core components of the intervention (fidelity). ^a^	Quantitative: A fidelity-adaptation tool Qualitative: Care Navigator implementation diaries, workshops, focus groups; and interviews with care navigators, providers and community members Timepoints: As per feasibility
Sustainability	The extent to which the Navicare intervention (or a modification of the intervention) was continued or planned to be continued at the end of the study, and barriers and facilitators of sustained use. ^a^	Quantitative: PSAT completed by Care Navigators and research staff Qualitative: Interviews with consumers and service users, field notes, project records and relevant documents Timepoints: Throughout the study period with PSAT completed at the end of one year of implementation at each site
Cost of implementation	The cost of implementing the Navicare service at each new site, including service costs, costs related to the implementation strategies used, and the location of the Navicare service. ^a^ The costs relating to both implementation strategies and intervention delivery will include salary, facilities, hiring, staff education and training, equipment, materials and resources	Quantitative: Navicare service data, project records, fidelity-adaptation tool, data obtained from health services databases (QHEDC & QHAPDC) Qualitative: Care Navigator implementation diaries, interviews related to cost and study activities Timepoint: Throughout the study period

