Cost of implementation will be evaluated across the study sites as well as for each EPIS phase and will include engagement of a local working group during preparation and implementation. Regression models will be used to explore the association between quantitative outcomes (for example, fidelity using the fidelity-adaptation tool with the implementation outcome of sustained access).

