#### Data collection

Local and district hospital level data from the Queensland Hospital Admitted Patient Data Collection (QHAPDC) and Queensland Hospital Emergency Department Data Collection (QHEDC) will be obtained for new sites for the 24-months prior to commencement, during the implementation period of 12-months, and for 12-months in the post-implementation (sustainment) period. The longer length of pre-implementation data will be used to account for seasonal patterns in this control period. For the existing site, QHAPDC and QHEDC data will be collected for 12-months pre-implementation to avoid, as much as possible, the major disruptions due to the COVID-19 pandemic in the first half of 2020, and for the implementation period will be collected from October 2021 when the first client accessed the service. Post-implementation data will be collected from July 2025 at the existing site.

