#### Data analysis

A* cost-consequence analysis* framework will be used to estimate the health service resource use and costs [55] associated with delivery of Navicare and associated implementation strategies [56] during the study period. Results will be descriptively summarised across disaggregated resource use and cost categories and presented alongside associated measures of program effectiveness to produce estimates of the ‘cost per service user’ and ‘cost per occasion of service’ to inform future planning and decision making. Uncertainty will be represented as 95% confidence intervals using non-parametric bootstrapping.

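### Hospital cost savings are estimated only for the sustainment period, while costs cover the whole study and the abstract promises value by EPIS phase

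*Protocol article*

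**What the plan says.** All references are to the protocol article.

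**Hospital consequences.** Economic evaluation methods, Data collection, names the item to be valued as "Potential cost savings from reduced emergency department presentations and overnight hospitalisations in the post-implementation period", which "will be estimated using an approach that is consistent with the effectiveness analysis".

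**What that period is.** Effectiveness study component methods, Data collection, obtains hospital data for new sites for 24 months before commencement, then "during the implementation period of 12-months, and for 12-months in the post-implementation (sustainment) period". Post-implementation is thus another name for sustainment and is listed apart from implementation. Aim 1 draws the same line when it compares the two periods. For the existing site the post-implementation data start in July 2025, with no stated length.

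**Costs.** Economic evaluation methods, Data analysis, covers resource use and costs "associated with delivery of Navicare and associated implementation strategies [56] during the study period". Table 1 gives the cost-of-implementation outcome as "Timepoint: Throughout the study period". The Data analysis section of the implementation component adds: "Cost of implementation will be evaluated across the study sites as well as for each EPIS phase".

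**What the abstract promises.** The Methods paragraph places the cost-consequence component in both the implementation and the sustainment phases, compared with pre-implementation data, with "value assessed for each EPIS phase using hospital, service, and resource allocation data".

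**The concern.** A cost-consequence analysis sets costs and consequences next to each other and leaves the reader to weigh them. That works only if both columns cover the same time. Here the cost column includes the implementation year and the hospital column, as worded, does not. Yet implementation begins, by the article's own definition of commencement, when the first client is seen at the site, and the sample size section expects about 13 to 17 new contacts per site per month in that phase. Hospital use could already be changing, in either direction.

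What is at stake is Aim 6. A decision maker would see at least two years of delivery cost beside one year of hospital savings at a new site, and could not obtain the result for the implementation phase that the abstract announces. If use falls in year 1, the table understates the benefit. If it rises, for instance because unmet need is newly identified, the table leaves out a cost.

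**Working it through.** The plan gives no figure to reproduce here, so the check compares time windows and then sizes the gap under stated assumptions.

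**Step 1: windows at a new site, side by side.**

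| Item | Exploration and preparation | Implementation (12 months) | Sustainment (12 months) | Source |
|---|---|---|---|---|
| Programme and implementation costs | counted | counted | counted | Economic Data analysis; Table 1; implementation Data analysis |
| Hospital data collected | yes, as part of the 24 pre-implementation months | yes | yes | Effectiveness Data collection |
| Hospital savings valued | comparison period | **not counted** | counted | Economic Data collection |
| Value by phase, per abstract | promised | promised | promised | Abstract, Methods |

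The gap is the implementation cell of the third row. Before commencement there is no client exposure, so the absence of a hospital effect there is expected.

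**Step 2: share of delivery time covered.** Delivery months = 12 + 12 = 24. Months with valued hospital savings = 12. Coverage = 12/24 = 50%.

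**Step 3: share of hospital change left out.** Let the monthly effect in sustainment be s and the average monthly effect in implementation be r × s. The article states neither, so r is an assumption.

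- Total change over delivery = 12rs + 12s
- Change captured by the sustainment-only window = 12s
- Share left out = 12rs / (12rs + 12s) = r / (1 + r)

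| Assumed r | Captured | Left out |
|---|---|---|
| 0 (no effect until sustainment) | 12/12 = 100% | 0% |
| 0.5 (same as a linear build-up over year 1) | 12/18 = 67% | 33% |
| 1 (constant effect) | 12/24 = 50% | 50% |

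If r is negative, meaning that use rises during implementation and then falls, the sustainment-only figure exceeds the two-phase total and the rise appears nowhere in the valued consequences.

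**Step 4: which outputs are touched.** The two summary measures named in the economic Data analysis section are cost per service user and cost per occasion of service. Neither contains a hospital saving, so neither depends on the savings window. The effect is confined to the hospital lines and to their comparison with the cost lines.

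**Step 5: can it be repaired with the planned data?** Yes. Hospital data are obtained for both phases, and the effectiveness Data analysis section models monthly presentation and admission rates with a generalised linear mixed model, which can yield a separate contrast for each phase.

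**The case against.** The best reply is that the article as a whole already points to wider coverage. The abstract puts the component in both phases with hospital data, Table 1 lists both hospital collections as sources for the cost outcome, and hospital data are gathered during implementation. On that view one sentence in the economic section is loose and nothing is excluded. This stands in part: the finding is an inconsistency between the economic section and the abstract, not proof that the investigators will discard the implementation year. But the economic section is where the rule is set, and it names a period that the article elsewhere separates from implementation. It states a window; it does not leave one to a fuller plan.

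It can also be said that uptake is expected to grow, so that valuing savings later is reasonable, and that the analysis is descriptive with no net cost planned. The first is the r = 0 case, in which nothing is lost, but the plan does not commit to it. The second limits the consequence and is accepted.

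A reader might infer four stronger points that the document does not support:

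- *Only decreases would be counted.* The wording is one-directional, but the savings are called potential and are tied to a model that can show increases. No rule discards a rise.
- *Time in the emergency department must be costed because it is a co-primary outcome.* A cost-consequence analysis may report it in natural units, and costing it on top of presentations risks counting the same attendances twice.
- *Most of the exposure at the existing site is lost.* October 2021 to June 2025 is 45 months, but the length of that site's post-implementation window is not given, the study period has no dates, and Table 1 defines implementation cost for new sites. No proportion can be derived.
- *The headline ratios are biased.* They do not use hospital savings.

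**Conclusion.** The point holds in a limited form. As worded, the economic section values hospital savings in the sustainment period only, while costs run over the study period and by phase, and the abstract promises value for each phase with hospital data. At new sites the hospital window is 12 of 24 delivery months. The share of total hospital change left out is 0%, 33% or 50% when the implementation effect is assumed to be 0%, 50% or 100% of the sustainment effect; these are illustrations, since the article gives no effect size or cost. A rise in use during implementation would go unreported among the valued consequences. Neither co-primary analysis is touched, nor is either named cost ratio. The correction should be made because it bears directly on Aim 6 and the data for it are already planned.

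**What to change.** In Economic evaluation methods, Data collection, replace the sentence on potential savings in the post-implementation period with wording to this effect: the change in cost, whether an increase or a decrease, of emergency department presentations and overnight hospitalisations will be estimated separately for the implementation and sustainment phases, each against pre-implementation, using the mixed model of the effectiveness component.

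In the Data analysis section that follows, state that each estimate will be presented beside the programme and implementation costs of the same phase and site, and show exploration and preparation costs on their own lines. Time in the emergency department can be reported in natural units among the effectiveness measures and need not be costed.

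This brings the economic section into line with the abstract. It costs a change of wording and a little more analysis; no new data are needed at the new sites, because hospital data for both phases are already to be obtained.

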#### Data analysis

A* cost-consequence analysis* framework will be used to estimate the health service resource use and costs [55] associated with delivery of Navicare and associated implementation strategies [56] during the study period. Results will be descriptively summarised across disaggregated resource use and cost categories and presented alongside associated measures of program effectiveness to produce estimates of the ‘cost per service user’ and ‘cost per occasion of service’ to inform future planning and decision making. Uncertainty will be represented as 95% confidence intervals using non-parametric bootstrapping.

### Sample size estimates

Sample size for the co-primary outcome of sustained access has been pragmatically based on the monthly numbers of new people in contact with Navicare for mental health or wellbeing services in the implementation and sustainment phases. Pilot work at the existing study site conservatively indicates that approximately 17 new adults or carers with mental ill-health (or at risk of mental ill-health) will contact Navicare monthly during the implementation phase at the existing site and a new site of similar size. Extrapolating this level of access to two expected smaller sites, approximately 13 new adults or carers with mental ill-health are expected to contact Navicare monthly during the implementation period at each of these sites. Sustainment phase contact numbers are unknown in advance but we expect the number of new people with mental ill-health (or at risk of mental ill-health) contacting Navicare to increase or at least stay the same in the sustainment period compared to the implementation period across the sites. Based on these estimates we have 94% power to detect a 20% increase in new Navicare client contact numbers in the sustainment period compared to the implementation period using a one-sided test.

The number of service consumers and service provider participants in qualitative data collection involving community consultations, workshops, and interviews is difficult to determine in advance of the analysis which will be ongoing throughout the project. However, a minimum number of 20 service providers and 30 consumers across the study has been pragmatically determined for planning purposes and to ensure diverse stakeholder representation (see Table 2).

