#### Co-primary outcome

Our novel co-primary outcome measure of sustained access to Navicare was identified in our initial intervention co-design work with communities as being of great importance [9]. This outcome will be evaluated using the total number of new eligible persons with or at risk of mental ill-health or their carers who seek assistance from or through Navicare each month either directly or by provider referral. These data will be obtained from routinely collected Navicare service data. Access will be measured monthly across the study, comparing implementation (12-months) and sustainment (12-months) phases across all new sites, with commencement defined according to when the first client is seen physically at each new local site (see Fig. 2). We consider this outcome to bear similarity to Proctor’s outcome of equitable access, with access hypothesised to combine the outcomes of penetration, sustainability and fidelity [28].

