#### Data analysis

A pre-post comparison analysis will be used to examine if Navicare has a greater effect than any underlying secular trend. This will be achieved by fitting a generalised linear mixed model, to model the monthly rates of time in the emergency department (using a Gamma or normal distribution depending on the data), mental health emergency department presentations (using a Poisson distribution), and admitted overnight hospitalisations (using a Poisson distribution) [54]. Random intercepts will account for the non-independence of data from the same facilities. For sustained service access (co-primary outcome) and adoption, the trend before and after formal support for Navicare ends will be modelled (implementation to sustainment periods, Hypothesis 1). Residuals of the models used will be checked to assess the model’s validity, with histograms to check for bimodality and outliers, and with autocorrelation over time assessed with the Durbin Watson test, and adjustments for underlying trends and seasonality.

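### The 94% power fits a comparison of phase totals or averages, not a trend-adjusted change test, and the plan does not say which contrast, site set or one-sided alpha it belongs to

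*Protocol article*

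**What the plan says.** The protocol article, Sample size estimates, bases power for sustained access on monthly counts of new contacts. For the existing site and one new site of similar size it expects that "approximately 17 new adults or carers with mental ill-health (or at risk of mental ill-health) will contact Navicare monthly". For the two smaller sites it says that "approximately 13 new adults or carers with mental ill-health are expected to contact Navicare monthly during the implementation period at each of these sites". It then states "Based on these estimates we have 94% power to detect a 20% increase in new Navicare client contact numbers in the sustainment period", continuing "compared to the implementation period using a one-sided test". It gives no alpha, test, model or allowance for dispersion or trend.

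Data analysis, under the effectiveness component, describes how this outcome will be analysed: "For sustained service access (co-primary outcome) and adoption, the trend before and after formal support for Navicare ends will be modelled". A bracket in that sentence ties the model to Hypothesis 1. The paragraph ends by mentioning adjustment for underlying trends and seasonality. Data analysis under the implementation component says only that a regression model will be used.

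The aims, the hypothesis and Table 1 all describe a comparison of the sustainment period with the implementation period. The site set differs between sections. Co-primary outcome describes "comparing implementation (12-months) and sustainment (12-months) phases across all new sites", whereas Table 1 brings in the existing site's 12 months before sustainment, and the sample size section counts the existing site's contacts.

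Study design gives the possibility that uptake of service access will rise over time as one reason for choosing the design.

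**The concern.** The effect that is powered is a 20% difference between two 12-month periods. The described analysis models the trend on either side of the change between them. These can be the same test or very different ones, depending on which quantity is taken from the model. With 12 months on each side, a phase indicator is strongly collinear with calendar time, so a step adjusted for a linear trend is estimated far less precisely than a difference of period averages.

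This is a co-primary outcome. A reader who trusts 94% would take a null result as good evidence against a 20% rise. If the tested quantity is the trend-adjusted step, a true 20% rise would be missed about half the time or more. If it is the period average, power is adequate, but a positive result could simply be the start-up growth of a new service.

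**Working it through.** **Inputs.** Monthly rates are 17, 17, 13 and 13, the rate ratio is 1.20 and the test is one-sided (Sample size estimates). The phases are 12 and 12 months (Co-primary outcome). Assumptions: alpha of 5% or 2.5%, since none is stated; Poisson variance; no autocorrelation.

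**Step 1: expected contacts.**
- Four sites: 60 a month, so 60 × 12 = 720 in implementation and 720 × 1.2 = 864 in sustainment.
- Three new sites: 17 + 13 + 13 = 43 a month, so 516 and 516 × 1.2 = 619.

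**Step 2: reproduce 94% from phase totals.** SE = √(1/C1 + 1/C2) and power = Φ(ln 1.2 / SE − z), with ln 1.2 = 0.1823 and z = 1.645 or 1.960.
- Four sites: SE = 0.0505. 0.1823 / 0.0505 = 3.61, giving 97.5% (5%) or 95.1% (2.5%).
- Three new sites: SE = 0.0596. 0.1823 / 0.0596 = 3.06, giving 92.1% or 86.4%.

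Two of the four combinations come within two points of 94%: four sites at 2.5% and three new sites at 5%.

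**Step 3: add a linear trend and test the step.** This uses the expected information from a Poisson log-linear model on 24 monthly counts per site, with site intercepts, a phase step and a common linear trend. The truth is a 20% step on a flat background.

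The loss can be checked by hand. For 24 equally spaced months split in half, the variance of time is (24² − 1)/12 = 47.92, the variance of the phase indicator is 0.25, and their covariance is 12 × 0.25 = 3. So r² = 9 / (0.25 × 47.92) = 0.751, and the variance inflation is 1 / (1 − 0.751) ≈ 4.0. The SE therefore doubles, to 0.1009 (four sites) and 0.1192 (three).

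| Sites, one-sided alpha | Phase totals | Step, trend-adjusted | Step, slope change also fitted | Period average, segmented model |
|---|---|---|---|---|
| Four, 5% | 97.5% | 56.5% | 55.7% | 97.5% |
| Four, 2.5% | 95.1% | 43.9% | 43.1% | 95.1% |
| Three new, 5% | 92.1% | 45.4% | 44.7% | 92.1% |
| Three new, 2.5% | 86.4% | 33.4% | 32.7% | 86.4% |

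If the slope change is tested instead, and the 20% average rise builds up gradually, power is 58.9%, 46.4%, 47.5% and 35.3% in the same order.

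**Step 4: what the period average leaves in.** The midpoints of the two phases are 12 months apart. Steady growth of g per month with no change at the transition gives a ratio of phase averages of (1 + g)^12. Setting this to 1.20 gives g = 1.2^(1/12) − 1 ≈ 1.5% a month. Growth of that size alone would produce the effect the study is powered for.

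**Step 5: dispersion (assumed values).** Multiply the SE from step 2 by the square root of the dispersion. For four sites, dispersion 1.5 gives 90% (5%) or 84% (2.5%), and dispersion 2 gives 82% or 72%.

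**The case against.** The strongest reply is that nothing in the article names a step test. The hypothesis, the aims, Table 1 and the power statement all speak of one period compared with another. A period-average contrast answers that and can be taken from the same segmented model with no loss of precision. Fitting the trend does not in itself cost power; the loss depends on the quantity tested. The phrase about underlying trends and seasonality closes a sentence on model checking that also covers the hospital outcomes, so it is not a clear commitment to a common linear trend in the access model. All of this stands.

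The sponsor's method is also unknown. Four sites at one-sided 5% with dispersion of about 1.25 gives 94.4%. A total of 47 contacts a month (17 + 17 + 13) at 5% gives 94.0%, although the article describes no such site set. It therefore cannot be said that the calculation ignored overdispersion.

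A reader might infer that the planned analysis really has 33-57% power, or that 94% holds only for a trend-free comparison. The documents support neither. The first depends on a contrast and an alpha that they do not state, and its two ends come from combinations whose phase-total power is 86.4% and 97.5%, not 94%. The second is contradicted by the last column of the table.

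The reply does not remove the mismatch. The article ties this outcome and Hypothesis 1 to a trend model and quotes a power that a trend-adjusted level or slope test would not have. The contrast that does reach about 94% leaves in the growth that the design section allows for.

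**Conclusion.** The point holds in conditional form. The 94% is not an arithmetic error: it is about what a comparison of phase totals or averages gives under Poisson variance. It does not belong to a trend-adjusted change test. If the level change is the test, power for a 20% rise is 44-45% for the two combinations nearest the stated figure and 33-57% over both site sets and both alphas, before any overdispersion, autocorrelation or seasonal terms. If the period average is the test, power is 86-98% on the same assumptions, but the result does not separate sustained access from continuing growth. As written, a reader cannot tell which applies, because the contrast and alpha are not named and the sections disagree on whether the existing site is included.

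**What to change.** Name one primary contrast for Hypothesis 1, one site set (reconciling Co-primary outcome with Table 1 and Sample size estimates) and the one-sided alpha. Then restate power for that contrast, in one of two ways:

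- **(a) Phase-average ratio as primary.** Take it from the segmented model or from a model without a linear trend. Restate power using the dispersion seen in the existing site's monthly series. Report the level and slope changes as secondary, and say plainly that the primary contrast does not separate sustainment from ongoing growth.
- **(b) Trend-adjusted level change as primary.** Replace 94% with the recomputed power: about 45-57% at one-sided 5%, or 33-44% at 2.5%, before any overdispersion.

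Either way the cost is a recalculation and possibly a less favourable stated figure. Neither option needs extra sites or months.

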## Methods

### Study aims and hypothesis

#### Implementation component

Aim 1: Determine whether implementation of the Navicare model sustains access (co-primary outcome) to mental health services in rural and remote settings in the post-implementation period compared to the implementation period.Aim 2: Determine the success (or otherwise) of implementing, scaling up and sustaining Navicare in four regional communities, and likely mechanisms of action.Aim 3: Understand the core and adaptable components of the Navicare model and implementation strategies across the study and within four communities in the Greater Whitsunday Region, Queensland.Aim 4: Provide conceptual evidence of the strengths and limitations of the EPIS framework when applied to rural and remote mental health in Australia and suggest refinement, complementary or alternate approaches for future studies.Hypothesis: The implementation of Navicare will sustain access (co-primary outcome) to mental health services in local rural and remote settings in the post-implementation period compared to the implementation period.

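### The co-primary hypothesis is that access is sustained, but the only test and power stated for it are for a one-sided increase

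*Protocol article*

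**What the plan says.** Under Study aims and hypothesis (Implementation component), Aim 1 and the only hypothesis concern maintenance: "The implementation of Navicare will sustain access (co-primary outcome) to mental health services in local rural and remote settings in the post-implementation period", with the implementation period as comparator.

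The Sample size estimates section says that sustainment numbers are not known in advance, but expects the number of new people "contacting Navicare to increase or at least stay the same in the sustainment period". It then states what the study is powered for, at 94%: "detect a 20% increase in new Navicare client contact numbers in the sustainment period compared to the implementation period using a one-sided test".

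Two other places describe the analysis of this outcome. Data analysis under the implementation component names a regression model. Data analysis under the effectiveness component says that the trend before and after formal support ends will be modelled, and ties this to Hypothesis 1. Neither gives a direction of test, an alpha or a rule for success.

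**The concern.** A claim that access is sustained is a claim that it has not fallen by an amount that matters. A one-sided test for an increase has no increase as its null, so full maintenance counts as a null result. The protocol therefore treats unchanged access as a good outcome in its hypothesis and expectation, but as a non-finding in its stated test.

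If that test decides the matter, two misreadings are open. A service that holds its access could be reported as having failed. Or a non-significant result could be reported as sustained access, although it would be equally compatible with a decline. The reading has consequences: under Scaling up, the scalability strategy is to be developed only if the evidence supports success in line with the study aims.

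**Working it through.** **Inputs**
- Monthly new contacts (Sample size estimates): 17 at the existing site, 17 at one new site of similar size, and 13 at each of two smaller sites. Four sites: 17 + 17 + 13 + 13 = 60. Three new sites: 17 + 13 + 13 = 43.
- Periods of 12 and 12 months (Co-primary outcome). Expected implementation contacts: 60 × 12 = 720, or 43 × 12 = 516. Both are used because the Co-primary outcome section compares the new sites, while Table 1 also brings in the existing site.
- Alpha is not stated. Assumed one-sided 5% (z = 1.645) or 2.5% (z = 1.960).
- No margin is stated. Ratios of 0.80, 0.85 and 0.90 are used for illustration only.
- Variance is Poisson, with no trend term, unless noted.

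**1. The plan's own figure.** Power = Φ( ln(RR) / √(1/m₁ + 1/m₂) − z ), with m₂ = RR × m₁ and RR = 1.20.
- Four sites: ln 1.20 = 0.1823; √(1/720 + 1/864) = 0.0505; ratio 3.61. Power 97.5% at 5%, 95.1% at 2.5%.
- Three sites: √(1/516 + 1/619.2) = 0.0596; ratio 3.06. Power 92.1% at 5%, 86.4% at 2.5%.

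The stated 94% is not matched exactly, but it lies within two points of two of these variants (95.1% and 92.1%). A plain one-sided test for an increase is thus a fair reading of the power statement.

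**2. The same test when access is maintained.** At RR = 1.00 the formula gives Φ(−z) = alpha. The test is significant 5% or 2.5% of the time and non-significant 95% or 97.5% of the time. This holds for any sample size, set of sites or variance, provided the test keeps its level.

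**3. Small true rises.**

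| True ratio | Four sites, 5% / 2.5% | Three sites, 5% / 2.5% |
|---|---|---|
| 1.05 | 24% / 15% | 20% / 12% |
| 1.10 | 58% / 46% | 47% / 35% |

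**4. The observed ratio needed for significance.** exp( z × √(2/m₁) ) gives 1.09 (5%) or 1.11 (2.5%) for four sites, and 1.11 or 1.13 for three.

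**5. A test that matches the hypothesis.** Non-inferiority with true ratio 1.00: power = Φ( −ln(margin) / √(2/m₁) − 1.960 ) at one-sided 2.5%. The standard error is √(2/720) = 0.0527 or √(2/516) = 0.0623. For margin 0.80 and four sites: 0.2231 / 0.0527 − 1.960 = 2.27, which gives 98.9%.

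| Margin | Four sites | Three new sites |
|---|---|---|
| 0.80 | 98.9% | 94.8% |
| 0.85 | 87% | 74% |
| 0.90 | 52% | 39% |

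**6. Sensitivity to overdispersion.** With an assumed variance inflation of 2 and margin 0.80, the standard errors become √(4/720) = 0.0745 and √(4/516) = 0.0880. Power falls to about 85% (four sites) or 72% (three).

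**The case against.** The strongest reply is that the one-sided test appears only in the power paragraph, which describes the sample size as pragmatic. The analysis sections speak of a regression and a modelled trend, with no pass or fail rule. The article is condensed, and a margin, an alpha and an interval convention may well stand in the full protocol or analysis plan. Their absence here is not a defect. All of this stands, and it is why the 95% to 97.5% figure is conditional on the stated test being used to judge the hypothesis.

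Three stronger readings are tempting, and the document does not support them.
- A reader might infer that the co-primary analysis cannot answer its question or cannot reveal a decline. The modelled trend can estimate change either way. On the same Poisson counts, a one-sided test for a fall would have about 98% to 99% power (four sites) or 92% to 96% (three) against a true ratio of 0.80.
- A reader might infer that contacts must rise by 20% for success. That figure is the alternative used for power. An observed rise of roughly 9% to 13% would be significant.
- A reader might infer that a margin of 0.80 is known to be feasible or acceptable. Its power depends on the absence of overdispersion, and nothing in the document says that losing a fifth of contacts would still count as sustained.

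It is also fair to say that significance with probability alpha at a ratio of 1.00 is true of any valid superiority test. That is the point: such a test does not fit this hypothesis. What survives is a conflict between two statements that the article itself makes. A margin set elsewhere would still leave the published power attached to a different hypothesis.

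**Conclusion.** The concern holds in a limited form. The hypothesis is maintenance, while the only stated test and power are for an increase. Judged by that test, exactly maintained access would be non-significant about 95% to 97.5% of the time, on an assumed one-sided alpha of 5% or 2.5%, and a non-significant result would be no evidence of maintenance. The mismatch itself needs no variance assumption; the power figures for small rises and for non-inferiority rest on Poisson variance without trend terms. The data and the regression are not at fault. Because this governs what can be concluded on a co-primary outcome, it should be put right before sustainment data are seen.

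**What to change.** Bring the sample size section into line with the hypothesis:
1. Declare access sustained if the lower bound of the two-sided 95% confidence interval (one-sided 97.5%) for the sustainment-to-implementation rate ratio exceeds a stated margin. Fix the margin before any sustainment data are seen, with a justification from the sponsor and community partners.
2. If that is met, test for an increase (ratio above 1) second, in fixed sequence. This needs no further alpha and keeps the interest in growth.
3. Report the two-sided 95% interval in every case, so that a decline is visible.
4. Restate power at a true ratio of 1.00, with the alpha, the sites counted, and an allowance for overdispersion, autocorrelation and trend terms.

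The cost is agreement on one margin and revised wording in the sample size section, and in the registration if it carries the same statement. The change of test calls for no additional data items. The downside is that the stated power may become less favourable: at a margin of 0.90 it is only 52% or 39% even under pure Poisson variance.
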